### Study outcomes

Table 2 outlines the study aims, relevant cohorts, and study outcomes.

**Table 2 Tab2:** Overview of TAIPAN research aims, study cohorts involved and outcome indicators

	Cohort(s)	Outcome indicators
Primary aim		
Determine the relationship between viraemia and incidence of new HIV infections among gay and bisexual men	Negative Positive	• HIV incidence • Viraemia prevalence
Secondary aims		
1. Assess the association between changes in guidelines and policies and earlier uptake of HIV treatment among gay and bisexual men	Positive	• Incidence of treatment initiation
2. Identify incidence and predictors of repeat HIV testing among HIV negative gay and bisexual men	Negative	• Incidence of repeat testing (second HIV test within a 12 month period)
3. Identify incidence and predictors of supressed HIV viral load among HIV positive gay and bisexual men	Positive	• Incidence of viral suppression

#### Outcome 1

The community prevalence of viraemia is defined as the proportion of gay and bisexual men (diagnosed and undiagnosed) with a viral load of ≥200 RNA copies/mm^3^. A viral load of ≥200 was selected as this is a commonly-used clinical marker of viral suppression and a recent meta-analysis found no transmission of HIV among individuals with less than 200 RNA copies/mm^3^ [14]. Community prevalence of viraemia was selected as it has been demonstrated to have the strongest correlation with HIV incidence over other measures (e.g., mean viral, treatment coverage) [15]. Our measure of viraemia will comprise the following four components:Annual prevalence of viraemia: will be calculated within the positive cohort using the annual prevalence of viral load test results of ≥200 RNA copies/mm^3^ (‘viraemia’) at each patients last viral load test within a calendar year. We will conduct sensitivity analyses to include any viral load test ≥200 RNA copies/mm^3^ in a year and also using a higher threshold of ≥1000 RNA copies/mm^3^.Annual prevalence of diagnosed HIV infection among gay and bisexual men: will be estimated using population prevalence techniques developed by and used for Australia’s national HIV surveillance [6]. This approach produces a prevalence estimate using data on HIV diagnoses from Australia’s National HIV Registry, adjusting for duplicate entries, deaths, and migration outside of Australia. For this estimate we will focus on HIV diagnoses where homosexual contact is identified as the route of transmission.Annual prevalence of undiagnosed HIV infection among gay and bisexual men: will be estimated using standard back-project models [16] and validated against a separate bio-behavioural survey conducted in 2013–2014 and to be repeated in 2017 [17].Prevalence of viraemia in gay and bisexual men with undiagnosed HIV infection: will be calculated using an estimate of undiagnosed infection obtained from the back-projection models coupled with the assumption that all undiagnosed men have viral loads of ≥200 RNA copies/mm^3^. We will also consider different viral load levels among undiagnosed men by using data from the National HIV Registry and stratifying viral load at diagnosis by HIV testing history (i.e., reported time since HIV test prior to diagnosis).

The combination of these components to generate community viral load is depicted in Fig. 1. We will calculate an annual community prevalence of viraemia in gay and bisexual men (diagnosed and undiagnosed) by combining (i) the annual prevalence of viraemia among those who have been diagnosed with the estimates of HIV prevalence, and (ii) the annual prevalence of viraemia among undiagnosed men with the estimates of undiagnosed infections.

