**Methods:**

Over the period 2009 to 2017, we will establish two cohorts making use of clinical and laboratory data electronically extracted retrospectively and prospectively from 73 health services and laboratories in the states of New South Wales and Victoria. The ‘positive cohort’ will consist of approximately 13,000 gay and bisexual men (>90% of all people living with HIV). The ‘negative cohort’ will consist of at least 40,000 HIV-negative gay and bisexual men (approximately half of the total population). Within the negative cohort we will use standard repeat-testing methods to calculate annual HIV incidence. Community prevalence of viraemia will be defined as the proportion of men with a viral load ≥200RNA copies/mm^3^, which will combine viral load data from the positive cohort and viraemia estimates among those with an undiagnosed HIV infection. Using regression analyses and adjusting for behavioural and demographic factors associated with infection, we will assess the temporal association between the community prevalence of viraemia and the incidence of HIV infection. Further analyses will make use of these cohorts to assess incidence and predictors of treatment initiation, repeat HIV testing, and viral suppression.

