### Cohorts

Study cohorts will be established using de-identified data extracted from electronic patient medical records. These data will be collected via an existing health sentinel surveillance network of clinics and laboratories known as the *Australian Collaboration for Coordinated Enhanced Sentinel Surveillance of Sexually Transmissible Infections and Blood Borne Viruses* (ACCESS). The existing network will be expanded from 50 health services and pathology laboratories in New South Wales and Victorian to a total of 73, including: 39 publicly-funded sexual health clinics, 10 general practice clinics with medium to high caseloads of gay and bisexual men (50 or more patients per year), six hospital HIV outpatient clinics, four community-led HIV testing services, and 14 private and public pathology laboratories.

Expansion of the surveillance network will aim to capture 95% or more of all HIV viral load tests conducted in both states as well as 100% of HIV diagnoses. These targets will be achieved by recruiting all laboratories that conduct HIV viral load testing as well all reference laboratories responsible for confirmatory HIV Western Blot testing. Table 1 outlines the service types and criteria used to identify health services and laboratories relevant to TAIPAN.

**Table 1 Tab1:** Health service and pathology laboratory types and criteria for the TAIPAN project (*n* = 73)

	Health services	Pathology laboratories
Service types	Sexual health clinics (*n* = 39) General practice clinics (*n* = 10) Hospitals (*n* = 6) Community-led health services (*n* = 4)	Publicly-funded (*n* = 6) Private (*n* = 8)
Criteria (any)	≥50 HIV gay/bisexual men annually ≥20 HIV positive male patients annually ≥5 HIV diagnoses annually	Any confirmatory HIV testing Any HIV viral load testing

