### Participants

Using de-identified data extracted from ACCESS sites, two patient cohorts of gay and bisexual men will be established: one comprising HIV positive men (‘positive cohort’) and the other HIV negative men (‘negative cohort’). The positive cohort will consist of approximately 13,000 HIV positive gay and bisexual men (approximately 90% of all gay and bisexual men with HIV in both states) and the negative cohort will consist of at least 40,000 HIV negative gay and bisexual men (approximately half of the population).

Both cohorts will be limited to men aged 16 years and older for whom there is at least once record indicating a history of sexual contact with other men. Indicators of same sex contact can be behavioural (i.e., self-reporting same sex partners), identity-based (i.e., recorded sexual orientation as gay or bisexual), or procedural (i.e., collection of an anal swab for STI testing). The positive cohort will include patients recorded as HIV positive or those who receive an HIV diagnosis during the study period. The negative cohort will include patients whose first record of HIV testing during the study period is negative. If during the course of the study a person is diagnosed with HIV, they will be reclassified to the positive cohort. Follow-up during the study period will be based on records from the participating services as well as the pathology conducted by participating laboratories.

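### Outcome 1 gives all diagnosed men the viraemia of those tested in the year, with no check on untested men; the viral load unit also needs correcting

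*Protocol article*

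**What the plan says.** Study outcomes, Outcome 1, builds the annual community prevalence of viraemia from four components.

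- Viraemia among diagnosed men comes from the positive cohort, using the result "at each patients last viral load test within a calendar year".
- Diagnosed prevalence comes from the National HIV Registry, "adjusting for duplicate entries, deaths, and migration outside of Australia". No adjustment for being out of care or untested is listed.
- The two are joined by "combining (i) the annual prevalence of viraemia among those who have been diagnosed with the estimates of HIV prevalence".
- Undiagnosed men are estimated by back-projection and assumed to be all viraemic, with an alternative based on viral load at diagnosis.

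The sensitivity analyses for the first component are stated: "We will conduct sensitivity analyses to include any viral load test ≥200 RNA copies/mm^3^ in a year", and a higher threshold of 1000.

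Under Data analyses, this annual figure is the independent variable in the primary Poisson regression, and incidence is assumed to respond to the preceding year's value.

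The threshold is given per mm³ in the Abstract ("the proportion of men with a viral load ≥200RNA copies/mm^3"), in Outcome 1 and in Outcome 5.

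**The concern.** A diagnosed man without a viral load in the year has no last result, so he cannot enter the viraemia proportion. He is still counted in the registry estimate with which that proportion is combined. The calculation therefore gives him the viraemia of tested men. Men who go a year without a viral load may well be out of care and untreated, so this could set the exposure too low. If the untested share or its viraemia changes over 2009-2017, the trend could be wrong as well.

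This series is the exposure in the primary analysis, and no planned analysis would reveal the problem. Undiagnosed men get an explicit assumption and an alternative to it; diagnosed but untested men get neither. Outcome 5 has a rule for men with no viral load or only one, but Outcome 1 has none.

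A separate matter is the unit. Viral load is written in the same per-mm³ unit as the CD4 counts in the Background, and it sits in the definitions of both viraemia and suppression.

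**Working it through.** The article states no viraemia level, untested share or bias, so there is no figure to reproduce. What follows is an illustration.

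**Inputs**
- From the article: 12% of people living with HIV undiagnosed (Discussion); undiagnosed men all viraemic (Outcome 1).
- Assumed: untested share of diagnosed men u = 10%; viraemia among untested men vu = 60%, constant; viraemia among tested men vt falling from 30% to 8%.

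**Coverage figures do not supply u.** The target to "capture 95% or more of all HIV viral load tests conducted in both states" counts tests, not men. The cohort is put at "approximately 13,000 HIV positive gay and bisexual men (approximately 90% of all gay and bisexual men with HIV in both states". That implies 13,000 / 0.90 = 14,444 men with HIV, about 1,444 of them outside the cohort. The text does not say how many of those are undiagnosed, nor how many cohort members are tested in a given year.

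**Formula.** True viraemia among diagnosed men = (1 − u)·vt + u·vu. The planned measure is vt. Its error is vt − true = u·(vt − vu), which is negative (understatement) only if vu exceeds vt.

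**Diagnosed men, vu constant at 60%**
- Start: 0.9 × 0.30 + 0.1 × 0.60 = 33%.
- End: 0.9 × 0.08 + 0.1 × 0.60 = 13.2%.
- Relative fall: measured 1 − 8/30 = 73%; true 1 − 13.2/33 = 60%.
- Upper bound, vu = 100%: 37% to 17.2%, a fall of 54%.

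**Adding undiagnosed men (0.88 × diagnosed + 0.12, with the 12% held constant)**
- Measured: 0.88 × 0.30 + 0.12 = 38.4%; 0.88 × 0.08 + 0.12 = 19.0%; fall 50%.
- True: 0.88 × 0.33 + 0.12 = 41.0%; 0.88 × 0.132 + 0.12 = 23.6%; fall 42%.

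**Untested viraemia falling in proportion (60% to 16%)**
- End: 0.9 × 0.08 + 0.1 × 0.16 = 8.8%.
- Relative fall among diagnosed men: 1 − 8.8/33 = 73%, the same as measured.

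**The direction can reverse.** Let tested viraemia fall from 30% to 10%, the untested share from 20% to 10%, and untested viraemia from 80% to 40%. True viraemia is 0.8 × 0.30 + 0.2 × 0.80 = 40%, then 0.9 × 0.10 + 0.1 × 0.40 = 13%. The true fall is 27 points (67.5%) against 20 points (66.7%) measured.

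**Unit.** 1 mL = 1,000 mm³, so 200 copies/mm³ is 200,000 copies/mL and 1000 copies/mm³ is 1,000,000 copies/mL.

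**The case against.** A reader might infer that the method understates viraemia and exaggerates its decline. The documents do not support that as a statement of fact. Understatement needs untested men to be more often viraemic than tested men, which is plausible but not documented; if they were all suppressed, the measure would be too high. Exaggeration also needs the untested share and its viraemia to stay roughly constant. The Background describes widening treatment guidelines and the removal of barriers, so both could have fallen.

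Nor does a change in end-point ratios carry straight into the regression. With u and vu constant, true viraemia among diagnosed men in the illustration is 0.9·vt + 0.06, a linear transform. With a constant undiagnosed share, the coefficient on the measured exposure is 0.9 times the true one, with the same sign and test statistic. This stands, under those conditions.

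It can also be said that the combination is drawn in a figure not available here, that the text speaks of combining rather than multiplying, and that handling of missing results may be left to a fuller document. This stands only in part. The article itself fixes the measure, the source of the multiplier and the sensitivity analyses, and all of them depend on tested men. If the denominator were instead the whole positive cohort, untested men would count as not viraemic: 0.9 × 30% = 27% against 33%, and 0.9 × 8% = 7.2% against 13.2%. On the same assumptions that is also too low.

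Finally, counting untested men as viraemic unless an earlier result exists could create a false decline if it became the main rule. Extraction starts on 1 January 2009, so no earlier result exists for that year. This stands and shapes the remedy.

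On the unit, a literal reading is implausible because Outcome 1 itself presents 200 as a cut-off for viral suppression. It looks like a consistent slip, but it still sits in the outcome definitions.

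**Conclusion.** The concern holds in a limited form. The primary exposure assigns the viraemia of tested men to diagnosed men without a viral load in the year, and neither planned sensitivity analysis tests this. The level is understated if untested men are more often viraemic. The trend may be distorted either way, or hardly at all, depending on how the untested share and its viraemia move over 2009-2017. With 10% untested and a constant 60% of them viraemic, the relative fall including undiagnosed men is about 50% measured against 42% true. Those inputs are assumptions, apart from the 12% undiagnosed, which is an Australian figure for all people living with HIV. The sample size and power figures are not affected.

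The per-mm³ unit is wrong as written by a factor of 1,000. It should be corrected, but it does not suggest that the intended analysis uses a different cut-off.

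**What to change.** Keep the stated measure as primary. For each calendar year, report the share of diagnosed men with a viral load result. Add one sensitivity analysis that splits diagnosed men into tested and untested and reruns the primary regression with untested men set to:

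- (a) the tested prevalence, which is the present implicit assumption;
- (b) their last earlier result carried forward within a fixed window, only for years with a full look-back, so that 2009 is not inflated;
- (c) all viraemic, as an upper bound.

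State that untested men found by subtraction from the registry estimate include men whose tests were not captured or not linked, so (c) will tend to overstate viraemia.

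Separately, change copies/mm³ to copies/mL wherever the 200 and 1000 viral load thresholds appear: the Abstract, Outcome 1 and Outcome 5.

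The cost is a little more analysis on data already to be extracted, and bounds that rest on assumptions. No new data collection is needed.

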**Fig. 1 Fig1:**
[figure not shown]
Method for calculating the prevalence of HIV viraemia among diagnosed and undiagnosed gay and bisexual men

#### Outcome 2

HIV incidence will be calculated using repeat testing among the negative cohort, [18] which will consider patients with two or more HIV tests for whom the first test was negative. We expect that more than 80% of gay and bisexual men will have at least two tests over the study period. An incident infection will be defined as an HIV diagnosis following a negative test and time at risk will be calculated as the time between each patient’s first and last test or a patient’s first test and HIV diagnosis. The number of incident infections will be divided by the person time (in years) at risk.

#### Outcome 3

Data from the positive cohort will also be used to calculate the incidence of ART initiation (i.e., the point at which ART is initiated) with the follow-up period defined as the time after HIV diagnosis (person years of infection). This variable will be restricted only to men diagnosed with HIV during the study period.

#### Outcome 4

Data from the negative cohort will be used to calculate the incidence of repeat diagnostic HIV testing. The incident event is defined as the point at which a patient achieves a second HIV test within six weeks to 12 months of a previous test, with follow-up time defined as the period between a patient’s first HIV test and last clinical encounter. Follow-up time will cease if a patient has no recorded service event of any kind within a two year period but will resume at the point of future service events (i.e., reengages with a participating service). Follow-up will also cease if a patient is diagnosed with HIV.

#### Outcome 5

Among the positive cohort, the incidence of viral suppression will be calculated. Viral suppression is defined as two consecutive viral load tests of <200 RNA copies/mm^3^ separated by at least three months; the first test will be taken as the point of suppression for calculating time. This variable will only be calculated among patients with no history of previous treatment and will exclude those for whom there is no or only one viral load test result. We will conduct a sensitivity analysis with a higher viral load threshold of <1000 RNA copies/mm^3^.

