## Discussion

Although treatment as prevention has already been shown to be highly effective among serodiscordant couples, further evidence is required to determine its community-level impact on HIV incidence among gay and bisexual men. This issue is particularly relevant in the Australian context, where testing and treatment coverage is high but where there has been no decline in annual HIV diagnoses [6]. The two large cohorts established in this study will provide detailed information on the level of testing and treatment coverage that can be achieved and, in the turn, the impact on HIV incidence.

While clinical trial results and modelling studies have fostered optimism about the treatment as prevention’s public health potential, the ultimate reduction of incidence may be somewhat less than expected in gay and bisexual men [26]. In Australia, an estimated 12% of people living with HIV are undiagnosed [6] with the average time between infection and diagnosis estimated to be between two and three years [22]. Undiagnosed infections contribute disproportionately to HIV transmission due to higher viral loads and sexual practices [5]. It is, therefore, a key strength of this study that it will consider the roles of diagnosed and undiagnosed HIV in onward transmission among gay and bisexual men.

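### The undiagnosed part of the viraemia exposure is back-projected from HIV diagnoses, most of which are also outcome events, so part of the primary association may be mathematical coupling

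*Protocol article*

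**What the plan says.** All references are to the protocol article.

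- **Exposure (Study outcomes, Outcome 1).** The annual number of undiagnosed infections "will be estimated using standard back-project models [16] and validated against a separate bio-behavioural survey", with survey rounds in 2013–2014 and 2017. Viraemia in these men rests on the "assumption that all undiagnosed men have viral loads of ≥200 RNA copies/mm^3", so in the main definition the back-projected count enters the exposure one for one. The last step combines "the annual prevalence of viraemia among undiagnosed men with the estimates of undiagnosed infections" with the corresponding figure for diagnosed men, which uses measured viral loads.
- **Outcome (Study outcomes, Outcome 2).** "An incident infection will be defined as an HIV diagnosis following a negative test". Time at risk ends at the diagnosis or the last test.
- **Model (Data analyses).** Viraemia enters a random effects Poisson regression as one value per calendar year, and incidence is taken to depend on the value of the year before.
- **Overlap (Cohorts; Sample size).** The network aims to hold every HIV diagnosis in the two states. Of 420 men diagnosed per year, 80% are expected to have a testing history and are counted as incident cases.
- **Delay and undiagnosed share (Discussion).** Infection precedes diagnosis by two to three years on average, and "an estimated 12% of people living with HIV are undiagnosed".

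**The concern.** A back-projected undiagnosed pool for year t−1 is reconstructed from men diagnosed in year t and later. Most of those men are also the events that the regression tries to explain. A random or real dip in diagnoses in year t therefore lowers the outcome of year t and, through the model, tends to lower the exposure assigned to year t−1. The two series then move together partly because they share data.

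The primary aim is a temporal association between viraemia and incidence. Coupling of this kind is expected to push that association in the hypothesised direction, and a reader of the main result alone could not tell how much of it arose this way. The measured component also shrinks as treatment expands, so the modelled component should weigh most in 2015–2017, the period the plan treats as full implementation.

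**Working it through.** **1. Overlap of the two data sources (plan's own figure).** 0.80 × 420 = 336, which reproduces the stated annual number of incident cases. The stated 80% power for a hazard ratio of 0.80 is also close: two successive years give 336 + 268.8 = 604.8 events, and Schoenfeld's formula at two-sided 0.05 (sidedness assumed) gives 78.3%. These figures are not in dispute. They show that about four in five diagnoses are expected to be outcome events.

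**2. Does the one-year lag separate them?** Assume an exponential delay with the plan's mean of two to three years.
- P(delay > 1 year) = exp(−1/mean): exp(−1/2) = 0.61 and exp(−1/3) = 0.72.
- So at least 61% to 72% of men diagnosed in year t were already infected at the end of year t−1. Back-projection places them in the undiagnosed pool of exactly the year paired with outcome year t. The lag does not break the link.

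**3. Weight of the undiagnosed component.** With 12% undiagnosed, all viraemic, and a proportion v of diagnosed men viraemic, the share is 0.12 / (0.12 + 0.88v).
- v = 0.34 (1 − 0.73 × 0.90: the plan's 73% on ART, with 90% of those suppressed as an assumption): 0.12 / 0.419 = 29%.
- v = 0.15 (assumed): 0.12 / 0.252 = 48%.
- v = 0.10 (assumed): 0.12 / 0.208 = 58%.
- Across 8% to 12% undiagnosed and 65% to 95% of diagnosed men suppressed, the share runs from 20% to 73%.

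**4. Part shared directly with the paired outcome year.** Under the same exponential delay, the fraction of the pool of year t−1 that is diagnosed in year t is 1 − exp(−1/mean): 0.28 (mean three years) to 0.39 (mean two years). Multiply by the share from step 3 and by the 80% that become outcome events:
- low: 0.29 × 0.28 × 0.80 = 0.065
- high: 0.58 × 0.39 × 0.80 = 0.18

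About 6.5% to 18% of the exposure is thus the same men as the paired outcome. Later diagnoses add indirect dependence that this does not count.

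**5. Direction.** A simulation (800 runs per setting) generated about 600 infections per year (420 / 0.7), independent of viraemia, with a known exponential delay and a smoothed back-projection. It compared eight lagged year pairs. With constant expected infections:

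| Mean correlation | Delay 2 y | Delay 3 y |
|---|---|---|
| Back-projected pool (t−1) with diagnoses (t) | +0.34 | +0.36 |
| Back-projected pool (t−1) with true new infections (t) | +0.08 | +0.06 |
| True pool (t−1) with true new infections (t) | −0.16 | −0.20 |

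The positive correlation appears when the outcome is the diagnosis series. In this setting only 4.9% and 5.6% of runs passed the two-sided 5% limit for eight pairs (|r| > 0.707). When infections varied independently by about 10% from year to year, the mean correlations were +0.48 and +0.43, and 19.8% and 13.9% of runs passed it. With trending infections the correlation was about 0.60 to 0.62, but part of that is shared trend.

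**6. Do the planned analyses address it?** Those under Outcome 1 change the threshold, the choice of viral load test, or the viral load level assumed in undiagnosed men. None changes the back-projected count.

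**The case against.** The strongest reply is that the article does not list the inputs or data cut-off of its back-projection. That is true: the use of later diagnoses follows from what the method is, not from a sentence in the text. The sentence containing "This approach produces a prevalence estimate using data on HIV diagnoses" does not fill the gap, because it describes prevalence of diagnosed infection.

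Several stronger readings are tempting and are not supported:

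- **That about half of the exposure is derived from the outcome.** The 48% to 58% is the undiagnosed share of viraemic men at assumed viraemia levels, with undiagnosed infection held at a figure for all people with HIV. The direct overlap is much smaller (step 4).
- **That the bias always favours the hypothesis, or that the regression would find an association without any effect.** The simulation covers only the undiagnosed component, aggregated by year. It omits measured viral loads, covariates, person-time and the multi-level model. It shows an expected direction, not a bias in the final estimate. Men who test often probably have shorter delays, which weakens the link.
- **That less testing would lower the outcome.** Outcome 2 is a rate and time at risk runs between tests, so less testing cuts person-time too.
- **That PrEP is ignored.** Covariates and Discussion plan to adjust for it. The adjustment acts on the outcome side, however, and does not alter a back-projected count that already reflects fewer diagnoses.

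The bio-behavioural survey also deserves credit. With rounds in 2013–2014 and 2017 it can check change as well as level, although two rounds cannot remove year-to-year dependence.

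**Conclusion.** The point holds in a limited form. Exposure and outcome draw on largely the same diagnoses, the one-year lag does not separate them, and no analysis described in the article changes the back-projected count. Part of the primary association may therefore be mathematical coupling, expected to favour the hypothesis, and its size in the final model is not known.

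The conclusion assumes that the back-projection uses diagnoses up to and beyond the outcome year, as the method normally requires. The figures further assume an exponential delay, the chosen viraemia levels in diagnosed men, a constant 12% undiagnosed, and that the plan's 80% applies to the men in question. This calls for a robustness check and an open statement of the dependence. It does not invalidate the primary exposure.

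**What to change.** - Prespecify a sensitivity analysis of the primary regression in which the exposure is measured viraemia in diagnosed men combined with diagnosed prevalence, and report it beside the main result. Diagnosed prevalence accumulates diagnoses already made, so those of year t do not feed back into the value for year t−1.
- State as a limitation that the undiagnosed component and the outcome share diagnosis data.
- Compare the change in the back-projected undiagnosed fraction between 2013–14 and 2017 with the change seen in the two survey rounds.

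The cost is one more model run and one comparison, on data already planned. The downside is that the diagnosed-only version leaves out undiagnosed men, who according to the Discussion contribute disproportionately to transmission. It should therefore not replace the primary exposure or act as a condition for claiming an association.

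Two other remedies are less suitable. Interpolating between the surveys cannot reach 2009–2012, which includes the whole before period. Cutting the back-projection off at year t−1 discards the diagnoses most informative about recent infection when the delay averages two to three years.
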